#### ChILI Patients:

Adults with cancer receiving checkpoint inhibitors (CTLA-4, PD-1 or PD L1 inhibitor) as monotherapy or combination (without chemotherapy) and developed acute liver injury secondary to checkpoint inhibitor and meeting the following criteria will be included:

1. Meets one of the following analytical thresholds at enrolment (visit 1)
  - Alanine transaminase (ALT) exceeding 5 times upper limit of normal (ULN) OR
  - ALT exceeding 3 times ULN plus bilirubin exceeding 2 times ULN OR
  - Alkaline phosphatase (ALP) exceeding 2 times ULN with accompanying elevations of gamma-glutamyl transferase in the absence of known bone metastases driving the rise in ALP level
2. Absence of other known causes of liver injury after detailed investigations

Patients who developed ChILI but did not meet the above criteria at enrolment or who were found to have different cause for their liver injury after further investigations will be excluded from analysis

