#### Sample size and justification

This is a mechanistic study to document the disease natural history rather than evaluate performance of specific biomarkers. As this uses specialist methods, we will only be able to recruit from a small number of suitable sites near to analytical facilities so sample size is limited by availability of suitable participants. Due to rarity of checkpoint inhibitors induced liver injury, incidence rate are between 3-18 % of patients receiving CPI, we aim to enrol 40 cases and 120 controls who received CPI without developing liver injury over 3 years. This is feasible at this centre based on current records of CPI treatment.

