## STATISTICS

### Statistical analysis

- We will calculate the incidence of ChILI and other irAE in the cohort group.
- We will describe demographic and clinical data for the enrolled participants using descriptive statistics, mean  $\pm$  standard deviation (SD) for continuous measurements and frequencies and percentiles for categorical data. We will compare patients' pathological and clinical characteristics using Chi-square test for categorical variables and Wilcoxon/Kruskal-Wallis test for the continuous variables.  $P < 0.05$  will be considered statistically significant.
- We will assess the accuracy of the biomarkers for ChILI detection and predicting prognosis using receiver operating characteristic (ROC) curve and the area under the ROC curve (AUC) with 95% confidence interval (CI).
- We will assess the correlation of biomarkers with ALT using Pearson's  $r$  coefficient.

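### The planned AUC for ChILI detection measures separation of injured from uninjured CPI patients, not diagnostic accuracy for ChILI as the cause; the correlation with ALT should be a within-case rank or log-scale one

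*Protocol*

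**What the plan says.** **Case definition** (Protocol, Eligibility criteria, ChILI Patients). A case must meet one of three laboratory thresholds at visit 1:
- on ALT alone: "Alanine transaminase (ALT) exceeding 5 times upper limit of normal (ULN) OR"
- on ALT with bilirubin: a lower ALT bar, 3 × ULN, provided that bilirubin is also more than twice its own limit;
- on ALP: "Alkaline phosphatase (ALP) exceeding 2 times ULN with accompanying elevations of gamma-glutamyl transferase", unless bone metastases explain it.

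The one element that is not a laboratory threshold is "Absence of other known causes of liver injury after detailed investigations". Study Treatment and Regimen adds that the thresholds must be met on the day of enrolment. Patients "found to have different cause for their liver injury after further investigations will be excluded from analysis".

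**Comparator** (Proposal Aims; Study Configuration, Part 3). Aim 2 compares ChILI patients with CPI-treated patients who had no liver injury. Part 3 sets case samples from the time of reaction against control samples from 6-14 weeks. The DILI and autoimmune hepatitis comparators in Part 4 are liver biopsies.

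**Analysis** (Statistical analysis). "We will assess the accuracy of the biomarkers for ChILI detection and predicting prognosis using receiver operating characteristic (ROC) curve", with the AUC and a 95% confidence interval. Then: "We will assess the correlation of biomarkers with ALT using" Pearson's r. The section names no transformation and does not say whether r is computed within cases or over all participants. For other continuous comparisons it uses rank tests.

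**Purpose of the sample size** (Sample size and justification). The study documents natural history "rather than evaluate performance of specific biomarkers".

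**The concern.** The same enzymes that define a case are absent, by selection, in the controls. Any marker that rises with ALT or ALP will therefore separate the two groups, whether or not it says anything about why the liver is injured. What makes an injury ChILI is that other causes are absent, and this contrast cannot test that: every patient with liver injury in the biofluid comparison is a ChILI case, and those found to have another cause are removed.

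At stake is how the result is read. An AUC reported as accuracy for ChILI detection, with a fairly narrow interval, invites use of the marker to tell ChILI from other liver injury in a CPI patient, which the data would not support.

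A smaller point is the correlation with ALT. If it is computed over cases and controls together, it partly repeats the case definition. If it is computed on untransformed skewed values, it can lose power.

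**Working it through.** The 40 cases and 120 controls rest on feasibility. The protocol gives no target AUC, r or power, so there is no stated figure to reproduce.

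**Step 1. AUC of ALT itself.** AUC = P(case value > control value), counting ties as one half. For cases entering on the first threshold, every ALT is above 5 × ULN. Controls have no liver injury, so none exceeds 5 × ULN. Hence AUC = 1.00 by definition. Cases entering by the ALT-plus-bilirubin or ALP route can overlap with controls on ALT. If 30% enter by the ALP route (an assumption), simulation gives about 0.98.

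**Step 2. A marker that only tracks ALT.** Assumptions, none of them in the protocol:
- control ALT: log-normal, median 0.6 × ULN, log-SD 0.45;
- case ALT: 5 × ULN × exp(E), with E exponential with mean 0.7;
- ALP-route ALT: log-normal, median 1.8 × ULN, log-SD 0.5, capped at 5 × ULN;
- marker = log ALT + normal noise, with noise SD = 0.6 × √(1/r² − 1) for a nominal within-group correlation r, and no ChILI-specific content;
- a hypothetical comparator of 40 patients with other-cause injury and the same ALT distribution as cases.

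Means over 600 runs:

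| Nominal r with log ALT | AUC v uninjured controls, no ALP-route cases | Same, 30% ALP-route | AUC v other-cause injury |
|---|---|---|---|
| 0.2 | 0.745 | 0.703 | about 0.50 |
| 0.3 | 0.844 | 0.784 | about 0.50 |
| 0.5 | 0.955 | 0.892 | about 0.50 |
| 0.7 | 0.995 | 0.949 | about 0.50 |

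**Step 3. Apparent precision.** Hanley-McNeil: Var(A) = [A(1−A) + (n₁−1)(Q₁−A²) + (n₂−1)(Q₂−A²)]/(n₁n₂), with Q₁ = A/(2−A) and Q₂ = 2A²/(1+A). At A = 0.80, n₁ = 40 and n₂ = 120: Q₁ = 0.667, Q₂ = 0.711, and Var = (0.16 + 1.04 + 8.46)/4800 = 0.00201. The half-width is 1.96 × 0.0449 = 0.088. At A = 0.90 it is 0.066. A marker with no information on cause could thus look both accurate and precise.

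**Step 4. Pooled correlation.** Assumptions: case ALT = 5 × ULN × exp(|N(0, 0.8)|), log-normal control ALT with median 0.6 × ULN, and a marker unrelated to ALT within each group but shifted upwards in cases. Share of studies with P < 0.05:

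| Shift in cases | Pooled Pearson, raw | Pooled Spearman |
|---|---|---|
| 1 log-SD | 91% (mean r about 0.29) | 97% |
| 0.5 log-SD | 44% | 51% |

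Within-case Spearman rejects in 5%, as it should. The artefact comes from pooling, not from the choice of Pearson.

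**Step 5. Power within 40 cases.** True log-scale correlation 0.45, with the case ALT model of Step 4, whose log-SD is 0.8 × √(1 − 2/π) = 0.48:

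| Marker log-SD | Raw Pearson | Spearman |
|---|---|---|
| 0.5 | 79% | 76% |
| 1.0 | 71% | 76% |
| 1.5 | 64% | 76% |

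The loss runs from none to about 12 points (76 − 64); a repeat run gave 14 (77 − 63). Larger losses (57% v 80%, 43% v 78%) appear only if ALT and marker both have log-SD 1.0 or 1.5, two to three times the spread of this ALT model.

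**The case against.** The strongest defence is that Aim 2 names exactly this contrast, ChILI against CPI-treated patients without injury, and that the primary outcome asks for biomarkers associated with the diagnosis. This stands. A reader might infer that the second primary outcome goes unanswered; it does not, because an association with liver injury under CPI is what the contrast estimates. What fails is only the further step to accuracy for ChILI as the cause.

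A reader might also infer that the protocol plans a pooled correlation on raw values, or offers r with ALT as evidence of diagnosis. It says neither. Population and transformation may be settled in an analysis plan that is not at hand, so the pooled results show what to rule out and not an error in the text. Nor is Pearson to blame for them, since pooled Spearman does worse. The skewness of the markers is likewise assumed.

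The argument has limits of reach. It does not apply to germline variants, prediction from pre-CPI samples, prognosis within cases, or the Part 4 histology, which does have DILI and autoimmune hepatitis comparators.

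Finally, removing misdiagnosed patients from the case group is sound practice. The exclusion criteria already bar those with a certain alternative explanation, so patients reclassified later would be few and selected. This is right, and it limits what that group can show. It is no reason to leave their data unreported. The sample-size sentence concerns the rationale for the numbers, so its conflict with the ROC plan is one of wording.

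**Conclusion.** The point holds in a bounded form. The AUC against uninjured CPI-treated controls measures separation of injured from uninjured patients and cannot support a claim of diagnostic accuracy for ChILI as the cause. For cases entering on ALT above 5 × ULN, the AUC of 1.00 for ALT follows from the definitions alone. The range of 0.70 to 0.995 for a marker that only tracks ALT, against about 0.50 with other-cause injury, rests on the assumed ALT distributions and on equal ALT in the two injured groups; its direction does not depend on the exact values. The case definition is mainly, not wholly, a matter of enzymes, because other causes must also be excluded.

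On the correlation, Pearson's r is named although the same section uses rank tests for continuous variables. A within-case rank or log-scale coefficient is the safer choice. The expected gain in power is modest, from none to about 12 points under the ALT model used here, and greater only with more skewness. The claim that genuine within-case correlations would generally be missed is not supported.

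**What to change.** In Statistical analysis:
1. Describe the AUC as discrimination from CPI-treated patients without liver injury, and report the AUCs of ALT and ALP beside it as reference.
2. Replace Pearson's r by Spearman's rank correlation, or by Pearson on log values, computed within ChILI cases and not pooled with controls.
3. Keep patients whose injury proves to have another cause out of the case group, but report those already enrolled and sampled descriptively as a separate comparator. Amend the exclusion sentence under ChILI Patients to allow this, and state that the group will be small and selected and its intervals wide.
4. Reconcile Sample size and justification with the ROC plan, for example by stating that the AUCs are descriptive and that the study was not sized for them.

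The cost is wording, a less favourable description of the AUC, and assays on a few extra stored samples. Recruitment and visits do not change.

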### Primary Outcome Measure

1. To estimate the incidence of checkpoint inhibitor-induced liver injury (ChILI) and other immune-mediated adverse reactions.
2. To identify and characterise biomarkers associated with the diagnosis of ChILI

### Secondary Outcome Measure

1. To identify risk factors and phenotypic features associated with ChILI and its association with other immune mediated adverse reactions.

2. To study the association between biomarkers, clinical features and development of ChILI.
3. To compare histological characteristics of ChILI with idiopathic auto-immune hepatitis and DILI due to other drugs.

## **ETHICAL AND REGULATORY ASPECTS**

### **Ethical Issues**

The study will not be initiated before the protocol, informed consent forms and participant information sheets have received approval / favourable opinion from a Research Ethics Committee (REC). Should a protocol amendment be made that requires REC approval, the changes in the protocol will not be instituted until the amendment and revised informed consent forms and participant information sheets have been reviewed and received approval / favourable opinion from the REC. A protocol amendment intended to eliminate an apparent immediate hazard to participants or researchers may be implemented immediately providing that the REC is notified as soon as possible and an approval is requested. Minor protocol amendments only for logistical or administrative changes may be implemented immediately; and the REC will be informed.

The study will be conducted in accordance with the ethical principles that have their origin in the Declaration of Helsinki, 1996; the principles of Good Clinical Practice and Good Laboratory Practice, the UK Department of Health Policy Framework for Health and Social Care, 2017 and in accordance with the Human Tissue Act, 2004.

### **Informed Consent and Participant Information**

The process for obtaining participant informed consent or consultee informed consent will be in accordance with the REC guidance, and Good Clinical Practice (GCP) and any other regulatory requirements that might be introduced. The investigator and the participant or their consultee shall both sign and date the Consent Form before the person can participate in the study.

The participant will receive a copy of the signed and dated forms and the original will be retained in the Study Master File. A second copy will be filed in the participant's medical notes and a signed and dated note made in the notes that informed consent was obtained for the study. Due to COVID-19 pandemic, we will also consider electronic consent (e-consent) through the secure website (REDCap) as a method of obtaining informed consent to reduce face to face contacts with patients.

The decision regarding participation in the study is entirely voluntary. The investigator or their nominee shall emphasize to them that consent regarding study participation may be withdrawn at any time without penalty or affecting the quality or quantity of their future medical care, or loss of benefits to which the participant is otherwise entitled. No study-specific interventions will be done before informed consent has been obtained.

If the Consent Form is amended during the study, the investigator shall follow all applicable regulatory requirements pertaining to approval of the amended Informed Consent Form by the REC and use of the amended form (including for ongoing participants).

### **Withdrawal**

The investigator will explain that participation in the study is entirely voluntary and that the participant will retain the right to withdraw at any time without prejudice by simply informing

the investigator. Should samples and data already have been obtained we will inform the participant that we would still like to use these samples and data and this will be indicated in the information sheet and consent form. Remaining tissue samples will be destroyed if the participant so wishes.

## **RECORDS**

Each participant will be assigned a trial identity code number for use on the CRFs, samples, consent forms and other trial documents and the electronic database.

CRFs will be treated as confidential documents and held securely in accordance with regulations. The investigator will make a separate confidential record of the participant's name, date of birth, local hospital number or NHS number, and Participant Study Number (the Study Recruitment Log), to permit identification of all participants enrolled in the trial, in accordance with regulatory requirements and for follow-up as required

CRFs shall be restricted to those personnel approved by the Chief or local Principal Investigator and recorded on the 'Study Delegation Log.'

All paper forms shall be filled in using black ballpoint pen. Errors shall be lined out but not obliterated by using correction fluid and the correction inserted, initialled and dated.

The Chief or local Principal Investigator shall sign a declaration ensuring accuracy of data recorded in the CRF.

## **Sample Labelling**

Each participant will be assigned a trial identity code number for use on the samples. Samples for NHS pathology analysis will be labelled in accordance with local NHS procedures.

## **Source documents**

Source documents shall be filed at the investigator's site and may include but are not limited to, consent forms, current medical records, laboratory results and records. A CRF may also completely serve as its own source data. Only trial staff as listed on the Delegation Log shall have access to trial documentation other than the regulatory requirements listed below.

## **Direct access to source data / documents**

Study documents, including progress notes and copies of laboratory and medical test results shall made be available at all times for review by the Chief Investigator, Sponsor's designee and inspection by relevant regulatory authorities.

## **Data Protection**

All study staff and investigators will endeavour to protect the study participants' rights to privacy and informed consent, and will adhere to the Data Protection Act, 2018. Only the minimum required information for the purposes of the study shall be collected. Documents will be held securely, in a locked room, or locked cupboard or cabinet. Access to the information will be limited to the study staff and investigators and relevant regulatory authorities (see above). Computer held data including the study database will be held securely and password protected. All clinical data collected from participants will be stored on a secure dedicated web server on the University of Nottingham REDCap platform. Access will be restricted by user identifiers and passwords (encrypted using a one-way encryption method).

Information about the study in the participant's medical records / hospital notes will be treated confidentially in the same way as all other confidential medical information.

Page 23 of 29

ChILI Protocol Final V1.6 / date 26/02/2024

|                                                                                                                                                                                                                                         |
|-----------------------------------------------------------------------------------------------------------------------------------------------------------------------------------------------------------------------------------------|
| This protocol is confidential and the property of the University of Nottingham. No part of it may be transmitted, reproduced, published, or used by other persons without prior written authorisation from the University of Nottingham |
|-----------------------------------------------------------------------------------------------------------------------------------------------------------------------------------------------------------------------------------------|

Only anonymised data will be shared outside the institution. A separate collaboration agreement will be in place describing the data to be shared with Pfizer. All data transfer outside the institution will be anonymised and via password protected encrypted files.

## **QUALITY ASSURANCE & AUDIT**

### **INSURANCE AND INDEMNITY**

Insurance and indemnity for study participants and NHS staff is covered within the NHS Indemnity Arrangements for clinical negligence claims in the NHS, issued under cover of HSG (96)48. There are no special compensation arrangements, but study participants may have recourse through the NHS complaints procedures.

The University of Nottingham as research Sponsor indemnifies its staff, research participants and research protocols with both public liability insurance and clinical trials insurance. These policies include provision for indemnity in the event of a successful litigious claim for proven non-negligent harm.

### **STUDY CONDUCT**

Study conduct may be subject to systems audit of the study files for inclusion of essential documents; permissions to conduct the study; CVs of study staff and training received; local document control procedures; consent procedures and recruitment logs; adherence to procedures defined in the protocol (e.g. inclusion / exclusion criteria, timeliness of visits); and equipment calibration logs.

### **STUDY DATA**

Monitoring of study data shall include confirmation of informed consent; source data verification; data storage and data transfer procedures; local quality control checks and procedures, back-up and disaster recovery of any local databases and validation of data manipulation. The Chief Investigator, or where required, a nominated designee by the sponsor or funder, shall carry out monitoring of study data as an ongoing activity.

Data entries will be verified by inspection against the source data. A sample (10% or as per the study risk assessment) will be checked on a regular basis for verification of all entries made. In addition, the subsequent capture of the data on any study databases will be checked. Where corrections are required these will carry a full audit trail and justification. Study data and evidence of monitoring and systems audits will be made available for inspection by the regulatory authority as required.

### **RECORD RETENTION AND ARCHIVING**

In compliance with the DH Research Governance Framework guidelines, the Human Tissue Act and in accordance with the University of Nottingham Code of Research Conduct and Research Ethics, the Chief Investigator will maintain all records and documents of the study. These will be retained for at least 7 years or for longer if required. We will be seeking consent to collate, store and use samples and data for a minimum of 10 years. If the responsible investigator is no longer able to maintain the study records, a second person will be nominated to take over this responsibility.

The study documents held by the Chief Investigator on behalf of the Sponsor shall be finally archived at secure archive facilities at the University of Nottingham. This archive shall include all study databases and associated meta-data encryption codes.

## **DISCONTINUATION OF THE STUDY BY THE SPONSOR**

The Sponsor reserves the right to discontinue this study at any time for failure to meet expected enrolment goals, for safety or any other administrative reasons.

## **PUBLICATION POLICY**

The clinical study report will be used for publication and presentation at scientific meetings. Investigators have the right to publish orally or in writing the results of the study. Participants will not be identified in any publications.

Summaries of results will also be made available to Investigators for dissemination within their clinical areas (where appropriate and according to their discretion). At the end of the study, we will disseminate findings to the public and provide study information and updates on our website and newsletter and at public engagement events.

